### Outcome measures

The primary outcome will be the hysterectomy rate at two years after endometrial ablation as treatment for HMB. This will be measured using questionnaires in the follow-up period and checked by consulting the individual participant file. Secondary outcomes will include women’s satisfaction (on a 6-point Likert scale), condition-specific quality of life and general Quality of Life, severity of cyclical and non-cyclical pelvic pain, presence of (inter)menstrual bleeding, non-hysterectomy reintervention rates (removal LNG-IUS, medical or other surgical interventions), number and type of complications and adverse effects of treatment. Costs will be evaluated from a societal perspective. Outcomes will be collected via an online questionnaire completed by participants and via an online Case Report Form (CRF) completed by researchers.

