#### Questionnaires for participants

Prior to treatment, participants will be asked to complete a baseline questionnaire containing a validated condition-specific quality of life measure Menorrhagia Multi-Attribute Scale (MMAS) as well as a validated EuroQol 5-level questionnaire [17–19]. The English language version of the MMAS questionnaire is shown in Additional file 1. Also, menstrual blood loss with a written Pictorial Blood Loss Assessment Chart (PBAC) score will be measured at baseline (Additional file 2) [20]. Participants will complete a questionnaire at six months follow-up asking about contraceptive use and smoking habits (Additional file 3). At 6-, 12- and 24-months participants will receive a questionnaire containing the MMAS questionnaire, the EQ-5D-5L questionnaire, and PBAC scoring, and questions on women’s satisfaction (6-point Likert scale), side effects of the LNG-IUS, and the presence of cyclic pelvic pain (pain score 0–10).

Societal costs (healthcare costs, lost productivity costs and informal care costs) are assessed using specifically adapted versions of the iMTA Productivity Cost Questionnaire (iPCQ) and the iMTA Medical Consumption Questionnaire (iMCQ) at 6, 12, 18 and 24 months (Additional file 4) [21, 22]. Participants will be asked to complete a menstrual calendar for one month to evaluate the intermenstrual bleeding 24 months after treatment (Additional file 5). An overview of questionnaires and timepoints is shown in Table 1.

**Table 1 Tab1:** Schematic overview of follow up questionnaires for participants

Timepoints	T_0_: Baseline	T_2_: 6 months	T_3_: 12 months	T_4_: 18 months	T_5_: 24 months
1. 6 months follow up questionnaire		x			
2. Women’s satisfaction		x	x		x
3. EQ-5D-5L	x	x	x		x
4. PBAC	x	x	x		x
5. Cyclic pelvic pain and MMAS	x	x	x		x
6. Side-effects or complications		x	x		x
7. iMCQ and iPCQ		x	x	x	x
8. Menstrual calendar					x

EQ-5D-5L = The 5-level EuroQol version of quality-of-life questionnaire, PBAC = Pictorial Blood Loss Assessment Chart, MMAS = menorrhagia multi-attribute scale questionnaire, iMCQ = iMTA Medical Consumption Questionnaire, iPCQ = iMTA Productivity Cost Questionnaire

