### Data-analysis

The primary analysis will evaluate if treatment of HMB by combined EA and LNG-IUS is superior to treatment by EA alone. The primary outcome measure will be a relative risk with 95% confidence interval and chi-squared test for hysterectomy at 24 months after treatment. The null-hypothesis is that combined endometrial ablation (EA) and LNG-IUS does not decrease the hysterectomy rate. The primary outcome will be analysed on the intention-to-treat population. Interim analyses will not be conducted.

Quality of life and longitudinal data on PBAC-scores will be analysed using Generalized Estimating Equations with treatment group, time, and treatment group—time interaction as variables, and a random effect for participants. Secondary outcomes that are dichotomous will be expressed as percentages and relative risks along with corresponding 95% confidence intervals. Calculating P-values will be based on the chi-square test or Fisher exact test, whichever is applicable. For continuous variables, the means will be presented along with the standard deviation, or the medians will be presented along with the interquartile range. Differences between the treatment groups will be estimated as differences in means of medians with t-test or Mann–Whitney test for inference (e.g. NRS-score pain). Questionnaires will be processed with the appropriate algorithms and presented by the usual methods (EQ5D and MMAS), with the baseline values adjusted for. Continuous data from questionnaires will be transformed or categorised as appropriate for the distribution of the data.

Quality-of-life data will be modelled using techniques that allow for missing data. Additional interventions or reinterventions can be obtained from medical files and will therefore have low rates of missing data. For remaining secondary outcomes measured using questionnaires, multiple imputation will be considered if necessary.

In addition to the analysis of the primary outcome on the intention-to-treatment population, the risk for hysterectomy will also be estimated for the per-protocol population.

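### The pain score is assigned to an unadjusted two-group test although Table 1 collects it at baseline, and the declared non-cyclical pain outcome has no listed instrument

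*Protocol article*

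**What the plan says.** All references are to the protocol article.

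- **Outcome measures** declares as a secondary outcome the "severity of cyclical and non-cyclical pelvic pain".
- **Questionnaires for participants**, running text, describes the pre-treatment step thus: "participants will be asked to complete a baseline questionnaire containing a validated condition-specific quality of life measure Menorrhagia Multi-Attribute Scale (MMAS"), together with the EuroQol questionnaire; PBAC is added in a later sentence. No pain score is named at baseline. At 6, 12 and 24 months the text lists "the presence of cyclic pelvic pain", scored 0–10.
- **Table 1**, row 5, "Cyclic pelvic pain and MMAS", is marked at baseline, 6, 12 and 24 months.
- **Electronic case report form for researchers** records pre-existing dysmenorrhoea at baseline, and complications and reinterventions later. It lists no pain score.
- **Data-analysis** has three relevant statements. The repeated-measures model is set out as "Quality of life and longitudinal data on PBAC-scores will be analysed using Generalized Estimating Equations". For continuous variables, "Differences between the treatment groups will be estimated as differences in means of medians with t-test" or its rank-based alternative, with pain as the example: "t-test or Mann–Whitney test for inference (e.g. NRS-score pain"). Questionnaires are to be "presented by the usual methods (EQ5D and MMAS), with the baseline values adjusted for".
- **Participants recruitment, randomisation and collection of data** stratifies randomisation by pre-existing dysmenorrhoea and by age around 45 years.

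**The concern.** Pain is one of the two symptoms that the Abstract and Background expect the LNG-IUS to prevent, so the pain comparison will be read closely. Pain shares a Table 1 row, and hence a schedule, with MMAS. Yet MMAS is adjusted for baseline and, as a quality-of-life measure, modelled over time, whereas pain is the named example for a simple two-group test. No reason is given. As worded, that test uses neither the baseline score nor the stratification factors, and does not combine the three follow-up scores. It also names no time point.

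Two inconsistencies bear on this. If sites follow the running text rather than Table 1, there may be no baseline score to adjust for. And an outcome is declared, non-cyclical pain severity, for which the article lists no measurement. A score not collected at a visit cannot be recovered later.

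**Working it through.** **1. The plan's own figure.** The article gives no power figure for pain; its only sample size is for hysterectomy. With 15% versus 8%, two-sided alpha 0.05, 80% power and unpooled variance:

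n per arm = (1.960 + 0.842)² × [0.15 × 0.85 + 0.08 × 0.92] / 0.07² = 7.849 × 0.2011 / 0.0049 = 322.1, rounded up to 323.

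That is 646 in total, and 646 / 0.90 = 717.8, so 718. Both agree with the article, and neither is in question. I use 323 evaluable women per arm below.

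**2. Which analysis covers which outcome.**

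| Outcome | Baseline in running text | Baseline in Table 1 | GEE | Named in baseline adjustment |
|---|---|---|---|---|
| EQ-5D | yes | yes | yes (quality of life) | yes |
| MMAS | yes | yes | yes (quality of life) | yes |
| Cyclic pain 0–10 | no | yes | no | no |
| Non-cyclical pain | not listed | not listed | no | no |

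**3. Precision given up on pain.** For one follow-up time, the variance of a baseline-adjusted difference relative to a follow-up-only comparison is 1 − r². The article gives no r, SD or target difference for pain, so r is assumed and the result is given in standard-deviation units.

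Unadjusted, the standardised difference with 80% power is 2.802 × √(2/323) = 0.220. With adjustment, the detectable difference is 0.220 × √(1 − r²), and power for a difference of 0.220 is Φ(2.802/√(1 − r²) − 1.960).

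| Assumed r | Variance factor 1 − r² | Equivalent gain in women, 1/(1 − r²) − 1 | Detectable difference | Power at 0.220 |
|---|---|---|---|---|
| 0.1 | 0.99 | 1% | 0.219 | 80% |
| 0.2 | 0.96 | 4% | 0.216 | 82% |
| 0.3 | 0.91 | 10% | 0.210 | 84% |
| 0.4 | 0.84 | 19% | 0.202 | 86% |
| 0.5 | 0.75 | 33% | 0.191 | 90% |

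These figures cover baseline adjustment at one time point only. I have not quantified any further gain from the strata or from combining the three follow-up scores.

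**4. Non-cyclical pain.** The outcome list names two kinds of pain. The questionnaire text and Table 1 list one, and the case report form items list none. No arithmetic applies; the sections disagree.

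**The case against.** The strongest reply is that nothing here is invalid. In a randomised comparison an unadjusted t-test or Mann–Whitney test is sound, pain is one of many secondary outcomes, and stratifying on dysmenorrhoea limits imbalance in a variable closely tied to baseline pain. That stands. A reader might infer a biased pain comparison, but the documents do not support it; the loss is one of precision.

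Second, the adjustment sentence begins with questionnaires in general, and the pain score is a questionnaire item. The bracketed EQ-5D and MMAS may qualify only how scores are presented. That reading is possible, but it does not displace the explicit naming of pain as the example for a t-test or Mann–Whitney test.

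Third, r has no source in the article. Both treatments are meant to change pain, so a weak correlation is plausible, and the gain could then be as small as 1% to 4%. That stands, and the size is stated accordingly.

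Fourth, this is a condensed article and its additional files are not shown. They may contain a non-cyclical item, and side effects are asked at 6, 12 and 24 months. A reader might infer that non-cyclical pain cannot be reported at all. That goes too far: the article shows only that no listed instrument measures it.

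A reader might also extend the criticism to PBAC, because its model lists no baseline covariate. PBAC is collected at baseline, and the model contains time and its interaction with treatment, so baseline may already enter as a time level. Nor does the article show that non-cyclical pain is the kind most likely to count against the device.

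**Conclusion.** The point holds as a matter of efficiency and consistency in a secondary outcome. The article assigns pain to an unadjusted test while scheduling a baseline score that could sharpen the comparison at no extra data cost. The gain is 9% to 25% of the variance if r is 0.3 to 0.5, and 1% to 4% if r is 0.1 to 0.2; all of these r values are assumptions. It also depends on the baseline score being collected as Table 1 shows, which is why the text and table must agree first.

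The mismatch over non-cyclical pain needs no assumption: it is declared in one section and absent from the instruments listed in the others. The wording inconsistencies are certain; the precision gain is real in direction but uncertain in size.

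**What to change.** 1. **Analysis.** Analyse the 0–10 pain score at 6, 12 and 24 months with the GEE approach already planned for quality of life, with the baseline pain score and the dysmenorrhoea and age strata as covariates. Report the adjusted difference with its confidence interval and keep Mann–Whitney as a sensitivity analysis. Correct the apparent slip of *of* for *or* between means and medians in the same sentence.
2. **Baseline pain.** Add the pain score to the baseline sentence of the questionnaire text so that it agrees with Table 1, and confirm that the item is in the baseline questionnaire in use.
3. **Non-cyclical pain.** Either list a 0–10 item for non-cyclical pelvic pain with its time points (baseline, 6, 12 and 24 months would match the cyclic item), or remove non-cyclical pain severity from the declared outcomes. If the additional files already contain such an item, naming it in the text and Table 1 is enough.

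Items 1 and 2 cost only wording, provided the baseline item is already in use. Item 3 costs at most one extra question per visit in an existing online questionnaire, and women already past a visit would lack that score. Removing the outcome costs a declared secondary outcome; the change should be documented and made before outcome data are examined by arm.

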## Statistical analysis

### Sample size

Based on a literature search of previous studies on hysterectomy rate after EA, we found variation in hysterectomy rates between 9 and 17.5% [3, 23–26]. An assessment in the Dutch population of hysterectomy rates after EA indicates a hysterectomy rate around 15% after previous EA in daily practice. For the sample size calculation, we assume a 15% hysterectomy rate after treatment with EA alone.

Based on a literature search on treatment with EA and LNG-IUS, we found two recently published studies with a comparable study population [15, 27]. These studies show hysterectomy rates after combined treatment between 0 and 11%. Therefore, in this study the hysterectomy rate in the group treated with EA and LNG-IUS is hypothesized to be 8% [15, 27]. Using an alpha of 0.05 and a beta of 0.2 and the 15% hysterectomy rate in the EA alone group and 8% in the EA + LNG-IUS group, 646 participants are needed to achieve 80% power. This enables the detection of a 7-percentage point’s difference between the group proportions. The sample size was calculated using the two-sided Z-Test with unpooled variance. Assuming a 10% loss-to-follow-up rate, we need to recruit 718 participants in the trial (359 per group). This sample size calculation was performed using PASS15.0.10.

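### The 0–10 pain score shares the visit schedule of the quality-of-life and PBAC measures but goes to an unadjusted two-sample test, which costs precision on a secondary outcome

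*Protocol article*

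**What the plan says.** Protocol article, Outcome measures: severity of pelvic pain, cyclical and non-cyclical, is a secondary outcome.

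Questionnaires for participants: the text describes a 0–10 pain score at 6, 12 and 24 months. In Table 1 the row "5. Cyclic pelvic pain and MMAS" is marked at baseline, 6, 12 and 24 months, as are the EQ-5D-5L and PBAC rows. The text listing the baseline instruments names MMAS, EuroQol and PBAC, but not pain.

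Data-analysis assigns methods as follows:
- "Quality of life and longitudinal data on PBAC-scores will be analysed using Generalized Estimating Equations", with group, time and their interaction.
- Questionnaire scores, with EQ-5D and MMAS named in brackets, are adjusted for baseline.
- Continuous variables are compared by a t-test or Mann–Whitney "test for inference (e.g. NRS-score pain". No baseline term, time term or time point is given for this comparison.
- For the remaining secondary questionnaire outcomes, multiple imputation is to be considered if needed.

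Randomisation is stratified by pre-existing dysmenorrhoea and by age around 45 years.

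**The concern.** The protocol does not leave the pain method open. It names one, and that method uses less of the data than the one given to instruments at the same time points, with no reason stated. Pain matters to the trial's rationale: the Background expects the LNG-IUS to suppress pelvic pain and to make haematometra less likely. The choice to stratify by dysmenorrhoea also implies that pain before treatment is thought to predict the later course.

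If baseline pain predicts follow-up pain, a comparison that ignores it reports a wider confidence interval than necessary and leaves any chance difference in baseline score in the estimate. The stake is the precision of one secondary comparison, obtainable at no cost if the baseline score is collected as Table 1 shows.

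**Working it through.** **The plan's own figure.** The article gives no power figure for pain, so the number of evaluable women comes from the primary outcome. Sample size states 15% and 8%, alpha 0.05, beta 0.2, and "The sample size was calculated using the two-sided Z-Test with unpooled variance".

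n per arm = (1.960 + 0.842)² × (0.15 × 0.85 + 0.08 × 0.92) / 0.07² = 7.849 × 0.2011 / 0.0049 = 322.1, so 323 per arm and 646 in total. Allowing for 10% loss, 646 / 0.9 = 717.8, so 718. Both match the article ("646 participants are needed to achieve 80% power"; 718 recruited, 359 per group).

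**Assumptions for pain.** The article gives neither the SD of the score nor the correlation r between baseline and follow-up. I take SD = 2.5 points and r = 0.3, 0.5 and 0.6, with 323 per arm evaluable.

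**Two-sample test at one visit.** Detectable difference at 80% power = 2.80 × 2.5 × √(2/323) = 0.55 points (0.22 SD).

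**The same visit adjusted for baseline.** The variance is multiplied by 1 − r² and the detectable difference by √(1 − r²). The equivalent total for an unadjusted test is 646 / (1 − r²).

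| r | 1 − r² | Variance reduction | Detectable difference | Unadjusted total needed to match 646 | Power for 0.2 SD |
|---|---|---|---|---|---|
| no adjustment | 1 | – | 0.55 | 646 | 72% |
| 0.3 | 0.91 | 9% | 0.53 | 710 | 76% |
| 0.5 | 0.75 | 25% | 0.48 | 862 | 84% |
| 0.6 | 0.64 | 36% | 0.44 | 1010 | 89% |

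The 0.2 SD difference (0.5 points at SD 2.5) is only illustrative.

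**What the repeated visits add.** If the effect were averaged over the three follow-ups, with baseline as covariate and an equal correlation r between all visits, the variance factor would be (1 + 2r)/3 − r². At r = 0.5 that is 0.667 − 0.25 = 0.417. This is a different target from the 24-month difference. For the 24-month contrast, a model with a separate group effect at each visit gains little from the 6- and 12-month scores when data are complete. The gain then comes mainly from baseline, and otherwise from women whose 24-month score is missing. The table is therefore the fair measure of the loss.

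**The case against.** **Baseline pain may not exist.** The T0 mark sits in a combined row and could belong to MMAS alone, and the text does not list pain at baseline. This stands. The table above applies only if the score was collected, and the document does not settle that.

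**The size is assumed.** This also stands. At r = 0.3 the gain is 0.02 points on a 0–10 scale. Cyclic pain may also be undefined after hysterectomy, which the plan expects in 8% to 15% of women, so 323 scores per arm is optimistic. A smaller n raises every detectable difference but leaves 1 − r² unchanged.

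**The score may be skewed with many zeros.** The plan allows for Mann–Whitney, transformation or categorisation. That is a fair reason to keep a rank-based or categorised analysis in support, but it does not argue against using baseline.

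**Stratification already limits imbalance.** It does so for dysmenorrhoea as a yes/no factor, not for the score itself. An unadjusted test also takes no credit for the stratification in its standard error.

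**The baseline-adjustment sentence may cover pain.** It opens with questionnaires in general, but its bracket names only EQ-5D and MMAS, and the text has already sent pain to the two-sample tests.

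Two stronger readings are not supported. A reader might infer that pain is the only repeated outcome kept out of the longitudinal model. Table 1 shows satisfaction and side effects or complications also repeated at 6, 12 and 24 months, and Data-analysis does not name them for that model either. A reader might also infer that missing pain scores are ignored. Data-analysis says multiple imputation will be considered for such outcomes; that is conditional, but the issue is addressed.

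**Conclusion.** The point holds as a matter of efficiency on a secondary outcome. The planned test is valid, and neither the primary outcome nor the sample size is touched. What is lost is 9% to 36% of the variance for an assumed r of 0.3 to 0.6, or a detectable difference of 0.55 instead of 0.53 to 0.44 points at an assumed SD of 2.5 with 323 evaluable women per arm. Near r = 0.3 the loss is minor; at 0.5 or above it is worth avoiding. All of this depends on baseline pain having been recorded, on which the Questionnaires text and Table 1 do not agree.

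**What to change.** 1. In Data-analysis, take the pain score out of the two-sample sentence. Analyse the 0–10 score at 6, 12 and 24 months with the longitudinal model planned for quality of life, adjusted for baseline pain and the two stratification factors (dysmenorrhoea and age). Name the 24-month adjusted difference with its 95% CI as the main contrast.
2. Keep a rank-based or categorised analysis as a sensitivity analysis if the score is strongly skewed.
3. Make the Questionnaires text and Table 1 agree on whether pain is scored at baseline. If it was not collected, adjust for the dysmenorrhoea stratum instead. That factor is needed for randomisation and so should be available for every woman; the gain then depends on how well it predicts later pain.

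The cost is a change of wording before analysis, with no added data collection. If Table 1 is wrong on baseline pain, the fallback likewise needs no new data.

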#### Electronic case report form for researchers

Baseline demographic characteristics, medical history, pre-existing dysmenorrhoea and current use of hormonal medication are recorded by the physician/research nurse in the electronic CRF. In addition, findings of the ultrasound examination will be collected in the eCRF, specifically, the existence of myomas (number, type and size) and presence of possible signs of adenomyosis.

At 6 weeks and 24 months after intervention the research nurse/physician will record post-treatment complications (expulsion or removal IUS, endometritis, uterine infection, bleeding (> 500 ml), uterine perforation caused by IUS insertion or EA) and reinterventions (including hysterectomy, removal of IUS, re-ablation or medical treatment).

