The per-protocol population will evaluate all participants who have completed their treatment as randomised. Those who are randomised to endometrial ablation have undergone this treatment. Those who are randomised to endometrial ablation together with the placement of an LNG-IUS have this treatment and the IUS remained in situ for at least 6 months. P-values < 0.05 will be considered to indicate statistical significance. The analysis will be done using the software Statistical Package for the Social Sciences (SPSS, Inc., Chicago, IL, USA).

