### Harm

Adverse events (AE) are defined as specific undesirable experiences occurring to a subject during the study, which are defined as complications from the treatment. At 6 weeks, the following most common complications are assessed; expulsion or removal IUS, hysterectomy, endometritis, uterine infection, bleeding > 500 ml, uterine perforation caused by IUS insertion or endometrial ablation. Also, reinterventions will be assessed at 12 and 24 months in the CRF. All Serious Adverse Events (SAE) will be reported by the local investigator to the principal investigator. The principal investigator must report a SAE to an accredited METC within 15 days of receiving knowledge of it. For SAEs that result in death or are life-threatening, reporting will be expedited. An expedited report will be submitted not later than seven days after the investigator is informed of the adverse reaction.

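### The per-protocol set drops hysterectomies before month 6 from the EA + LNG-IUS arm only, which biases this supportive relative risk towards the combination; the intention-to-treat primary analysis is unaffected

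*Protocol article*

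**What the plan says.** The Outcome measures section sets the endpoint: "The primary outcome will be the hysterectomy rate at two years after endometrial ablation". Data-analysis gives the effect measure as a "relative risk with 95% confidence interval and chi-squared test for hysterectomy at 24 months after treatment", and names the main population: "The primary outcome will be analysed on the intention-to-treat population". It then adds that "the risk for hysterectomy will also be estimated for the per-protocol population".

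The end of Data-analysis defines that second population separately by arm. For EA alone: "Those who are randomised to endometrial ablation have undergone this treatment". For EA + LNG-IUS, women must "have this treatment and the IUS remained in situ for at least 6 months". A general significance rule of p<0.05 follows. No landmark is stated, and no matching post-procedure condition is set for controls.

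The article expects both kinds of early event. The Harm section lists, among the complications assessed at 6 weeks, "expulsion or removal IUS, hysterectomy, endometritis, uterine infection". The section on the electronic case report form records "reinterventions (including hysterectomy, removal of IUS, re-ablation or medical treatment".

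**The concern.** The 6-month in-situ condition lies inside the 24-month outcome window and applies to one arm. A hysterectomy ends the time that the IUS is in place. A combined-arm woman who has one at month 3 therefore fails the entry rule, and she and her event disappear. A control woman with the same event stays in and counts. Membership of one arm depends in part on being free of the outcome for 6 months (immortal time); membership of the other does not.

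The same condition drops combined-arm women whose IUS was removed or expelled early. They have no counterpart in the control arm, so this is a second, separate selection.

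At stake is the reading of a supportive analysis of the primary outcome. Readers will turn to it for the effect in women who keep the device. It could show a stronger benefit than intention-to-treat, or a benefit where there is none, because of how the set was built.

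**Working it through.** **Inputs from the article (Sample size).** Hysterectomy rates 15% (EA alone) and 8% (EA + LNG-IUS); two-sided alpha 0.05; power 80%; Z-test with unpooled variance; 10% loss to follow-up.

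**The article's own figure first.** n per arm = (1.960 + 0.842)² × (0.15×0.85 + 0.08×0.92) / 0.07² = 7.849 × 0.2011 / 0.0049 = 322.1, rounded up to 323, so 646 in total. 646 / 0.90 = 717.8, rounded up to 718. Both match the article. The 323 evaluable women per arm are used below.

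**Assumptions (not in the article).**
- f: share of the 24-month hysterectomies that occur before month 6, taken as 0 to 40%.
- r: share of combined-arm women who lose the IUS before month 6 without an early hysterectomy, taken as 0 or 10%.
- h: later hysterectomy risk in those women, taken as 5% or 30%.

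A constant hazard fixes one value of f: 1 − 0.85^(6/24) = 3.98% have a hysterectomy before month 6, so f = 0.0398/0.15 = 26.5%.

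**Formula under no effect.** With true risk p = 15% in both arms, the control per-protocol risk stays at p. The combined-arm per-protocol risk is

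[p(1 − f) − r·h] / [1 − p·f − r].

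**Early hysterectomies only (r = 0).** The chance of p<0.05 favouring the combination is by normal approximation, with 323 controls and 323 × (1 − p·f) in the combined arm.

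| f | Combined-arm risk | Control risk | RR | Chance of p<0.05 favouring the combination |
|---|---|---|---|---|
| 10% | (0.15 − 0.015)/(1 − 0.015) = 13.7% | 15% | 0.91 | about 7% |
| 26.5% | (0.15 − 0.0398)/(1 − 0.0398) = 11.5% | 15% | 0.77 | about 26% |
| 40% | (0.15 − 0.06)/(1 − 0.06) = 9.6% | 15% | 0.64 | 54–55% |

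The nominal chance is 2.5%. For the middle row: 323 × 0.9602 = 310 women remain; SE = √(0.1148×0.8852/310 + 0.15×0.85/323) = 0.0269; the difference is 0.0352; Φ(0.0352/0.0269 − 1.96) = Φ(−0.65) = 0.26. In the last row, 54% comes from a pooled and 55% from an unpooled standard error in the test.

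**Adding early IUS loss (r = 10%).**

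| f | h | Combined-arm risk | RR |
|---|---|---|---|
| 25% | 30% | 9.6% | 0.64 |
| 25% | 5% | 12.5% | 0.83 |
| 10% | 5% | 14.7% | 0.98 |
| 0 | 5% | 16.1% | 1.07 |

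Setting the formula below p shows when the net bias favours the combination: p·f(1 − p) > r(p − h). For r = 10% and h = 5%, that is f > 0.10×0.10/(0.15×0.85) = 7.8%. Below that share the direction reverses.

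**Under the planned effect.** With a constant hazard at 8%, 1 − 0.92^0.25 = 2.06% occur early. The combined-arm risk becomes (0.08 − 0.0206)/(1 − 0.0206) = 6.06%, so RR = 0.0606/0.15 = 0.40, where the true value is 0.08/0.15 = 0.53.

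**After the fix, with no effect.** If both arms are defined by treatment at the procedure, the comparison is 15% v 15%, RR 1.00. With a 6-month landmark in both arms and no other IUS loss, the risks are 13.7% in each arm at f = 10% and 9.6% in each at f = 40%, again RR 1.00.

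**The case against.** The strongest reply is that this analysis is additional. The primary analysis is intention-to-treat, and the sample size and the superiority conclusion do not depend on the per-protocol set. That stands, and it limits the severity. A reader might infer that the trial's main result is compromised; the article does not support that.

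Second, the size rests on quantities that the article does not give. That also stands. At a 10% early share the distortion is modest, and no figure above is a prediction. A reader might infer that the rule always favours the combination. That follows for early hysterectomies taken alone, but not once early IUS loss is included. The article gives neither the reasons for removal or expulsion nor the later risk of these women.

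Third, a minimum exposure to a device is a legitimate interest, and the authors may intend to keep early hysterectomies as events. The wording does not say so. Counting a hysterectomy with the IUS still in place as an event would remove most of the first bias, but would leave the one-sided selection through early removal and expulsion.

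Two further inferences should be resisted. Keeping controls who later receive an LNG-IUS does not favour the combination: if the device works, it pulls the comparison towards no difference; if it does nothing, it has no effect. Nor is the per-protocol analysis clearly the only other analysis of hysterectomy. The Subgroup analysis section plans interaction models and names no outcome, so the primary outcome may be meant.

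**Conclusion.** The point holds for the per-protocol analysis. As written, the entry rule is asymmetric and conditions one arm on an event-free period within the outcome window. With no treatment effect and no other IUS loss, any hysterectomy before month 6 moves the relative risk below 1: to 0.91, 0.77 and 0.64 for early shares of 10%, 26.5% and 40%. These figures assume 15% true risk in both arms and 323 evaluable women per arm. Early removal or expulsion strengthens the bias if those women are at above-average later risk. If their risk is low it weakens the bias, and reverses it where early hysterectomies are also few (RR up to about 1.07 in the range examined). The asymmetry is certain from the text; the magnitude is not. This should be fixed, but it does not put the intention-to-treat primary analysis in doubt.

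**What to change.** Replace the 6-month condition with one rule for both arms, based on treatment received at the index procedure: EA done, versus EA done with the LNG-IUS inserted, and no criterion after the procedure. All hysterectomies from the procedure to 24 months then count in both arms.

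If the effect in women who keep the device is wanted, add a separate analysis with a 6-month landmark in both arms: women free of hysterectomy at month 6, with events counted from month 6 to 24. Label it a non-randomised comparison, because selection through early IUS removal remains in one arm.

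The change is about one sentence in the analysis text, made before the data are analysed, and needs no new data. The price is that the per-protocol result will probably be less favourable to the combination, and that the main per-protocol set will reflect insertion of the device and not its continued use.
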